### Sample Size

Perceived stress is our primary outcome measure and is used for the power calculation. Based on the results of a previous study about an online intervention for carers [39], we expect an effect size (Cohen *d*) of 0.40. Assuming an alpha of .05 and a statistical power (1-beta) of .80 in a two-tailed test, we will need 100 respondents in each of the conditions, resulting in a total of 200 participants. Calculation of the sample size was carried out with G*Power 3.1.9.2 (Heinrich-Heine-Universität Düsseldorf) [40].

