### Statistical Analysis

We will first check whether or not the randomization was successful by comparing the two groups for all baseline variables with *t* tests for continuous data or chi-square tests for dichotomous data. We will also check for differences between study dropouts and those who remain in the study at 3 months. The primary analyses will be based on the intention-to-treat principle. Sensitivity analyses will be performed only with those participants that filled out the pre- and posttest questionnaires (ie, completers). Missing data handling will depend on the amount and pattern of missing data, selecting the most appropriate technique. We will use the generalized estimating equation to examine the association between changes in stress scores (ie, PSS scores) and treatment arms (ie, iSupport vs waiting list). We will correct for baseline scores if they are not equally distributed. We will examine the influence of age, gender, and relationship (ie, spouses vs other relationship) on the outcomes. These analyses will be repeated for burden, anxiety and depression, sense of competence, self-efficacy, and mastery. Next, we will express the between-group, posttest, effect sizes for the different outcomes using Cohen *d*. Cohen *d* is the difference between the two posttest means divided by the pooled standard deviation. An effect size of 0.8 is considered to be large, an effect size of 0.5 is considered to be moderate, and an effect size of 0.2 is considered to be small.

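### The reported Cohen d is defined from posttest means alone, without the baseline correction that the tested model may receive, so the two can disagree

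*Protocol article*

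**What the plan says.** All but one of the relevant statements are in the Statistical Analysis section of the protocol article.

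- Population: "The primary analyses will be based on the intention-to-treat principle". Completers appear only in a secondary role: "Sensitivity analyses will be performed only with those participants that filled out the pre- and posttest questionnaires (ie, completers".
- Model: "We will use the generalized estimating equation to examine the association between changes in stress scores (ie, PSS scores) and treatment arms".
- Baseline: "We will correct for baseline scores if they are not equally distributed".
- Missing data: "Missing data handling will depend on the amount and pattern of missing data, selecting the most appropriate technique".
- Effect size, after the model: "Next, we will express the between-group, posttest, effect sizes for the different outcomes using Cohen" d, which "is the difference between the two posttest means divided by the pooled standard deviation". Values of 0.8, 0.5 and 0.2 are then labelled large, moderate and small.

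The Sample Size section plans on the same scale ("we expect an effect size (Cohen" d of 0.40), with 100 carers per arm.

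**The concern.** The section describes two estimates of the treatment effect and does not connect them. The tested one concerns change from baseline and may be corrected for baseline. The reported one compares posttest means and is never corrected.

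The mismatch is largest when it matters most. If the arms differ at baseline, the plan treats this as reason to correct the model, yet d as written still carries the part of the imbalance that persists to T1. The p value and the effect size could then tell different stories, for example a clear model effect beside a d in a lower band, or the reverse. Because d is the only quantity given interpretive labels and is on the scale of the planning assumption, readers are likely to use it to judge how large the benefit is.

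**Working it through.** **Inputs.** From the article: 100 per arm, 1:1 allocation, planned d = 0.40, two-sided alpha 0.05, power 0.80. Not in the article, so assumed: pre-post correlation ρ of the PSS (0.5 to 0.7), equal SDs at baseline and T1, and every dropout rate below.

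**The plan's own figure.** The normal approximation gives n = 2(1.960 + 0.842)²/0.40² ≈ 98.1, so 99 per arm. The exact two-sample t test gives 99.08, rounded up to 100, with power 0.804 at 100. The stated 100 per arm reproduces.

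**Chance baseline imbalance.** In SD units, the difference between arms at baseline has SD √(2/100) = 0.141.

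**Posttest d against a baseline-adjusted d.** The adjusted estimate removes ρ times the baseline difference, so the gap has SD ρ × 0.141. The standard error of posttest d is about 0.141; that of the adjusted d is 0.141 × √(1 − ρ²).

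| Assumed ρ | SE, posttest d | SE, adjusted d | SD of gap | 95% range of gap | P(gap beyond ±0.10) |
|---|---|---|---|---|---|
| 0.5 | 0.141 | 0.122 | 0.071 | ±0.14 | 0.16 |
| 0.6 | 0.141 | 0.113 | 0.085 | ±0.17 | 0.24 |
| 0.7 | 0.141 | 0.101 | 0.099 | ±0.19 | 0.31 |

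A gap of 0.10 is a quarter of the planned 0.40.

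**Posttest d against an uncorrected change estimate.** If the GEE compares changes without baseline correction, the gap is the baseline difference itself: SD 0.141, 95% range ±0.28, whatever ρ is. The standard error of the change estimate is 0.141 × √(2(1 − ρ)), which is 0.141 at ρ = 0.5 and 0.110 at ρ = 0.7.

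**Example.** Take a true effect of −0.40, ρ = 0.6, and an intervention arm that starts one standard error (0.141) higher on stress. Expected values given that imbalance:

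- posttest d: −0.40 + 0.6 × 0.141 = −0.315
- adjusted d: −0.40
- change estimate: −0.315 − 0.141 = −0.456

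**Expectation and dropout.** A simulation (1,500 trials per scenario, 100 per arm, true effect −0.40, ρ = 0.6) compared d from observed posttest scores with a baseline-adjusted regression standing in for an adjusted model. In the last three rows, dropout in the intervention arm depends on baseline stress and dropout in the control arm is random.

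| Assumed dropout, intervention / control | Posttest d, observed cases | Adjusted |
|---|---|---|
| None | −0.394 | −0.398 |
| 20% / 20%, random | −0.408 | −0.403 |
| 30% / 15%, higher-stress carers leave | −0.539 | −0.406 |
| 40% / 20%, higher-stress carers leave | −0.584 | −0.406 |
| 40% / 20%, lower-stress carers leave | −0.239 | −0.406 |

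There is no systematic gap in the first two rows. One of about 0.13 to 0.18 appears in the other three, and only because d was computed there on observed cases.

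**The case against.** The strongest reply is that d is a descriptive standardization added after the model. No test or success criterion rests on it, and posttest difference over pooled SD is a standard, transparent definition. It is also the quantity that an unadjusted two-sample sample size calculation assumes. All this is true, and it keeps the point away from the primary test.

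Three stronger readings are tempting, and the article does not support them:

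- **That d is the headline result.** The text does not say so, and it states no comparison of the observed d with 0.40.
- **That d leaves out non-responders.** The text names no population for the posttest means. Completers are confined to sensitivity analyses and the missing-data technique is open, so imputed or model-based means would fit the wording. The dropout bias above is therefore conditional. The article says only that minimal support might raise dropout and gives no rate or pattern.
- **That d will not match the model.** The two agree in expectation without informative dropout. They may differ in any one trial.

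A further fair objection concerns precision. The gain in the first table is against a model that always adjusts for baseline, whereas the plan adjusts only conditionally. Against an uncorrected change analysis, posttest d is no less precise at ρ = 0.5, and more precise below that. This stands, and it is why the fix has to settle the baseline rule as well.

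The reply does not remove the baseline mismatch. It follows from a formula that the article fixes, and it does not depend on missing data.

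**Conclusion.** The point holds as a matter of consistency and precision. The plan may correct the tested estimate for baseline but defines the labelled effect size so that it cannot be. At 100 per arm, chance imbalance alone separates posttest d from a baseline-adjusted d with an SD of about 0.07 to 0.10, and by more than 0.10 in about 16% to 31% of trials, for assumed correlations of 0.5 to 0.7. Against an uncorrected change estimate the SD is 0.141. These figures rest on equal SDs and an assumed correlation, since the article gives neither.

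Bias is not shown: it would need d to be computed on observed cases and dropout to be differential and related to baseline, and the article states neither. The sample size and the primary test stand as they are.

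**What to change.** In the Statistical Analysis section, define d for each outcome as the baseline-adjusted between-arm difference at T1 from the intention-to-treat model, with its 95% CI, divided by a named SD such as the pooled baseline SD. State that the baseline score enters the model regardless of observed imbalance. Keep the unadjusted posttest d as a descriptive extra and name the population it uses.

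The cost is a few sentences. The baseline scores are already collected and no extra carers are needed, but the conditional baseline rule has to be replaced, which is a change to the model and not only to reporting. The adjusted d is slightly less directly comparable with published posttest d values, and the descriptive extra covers that.

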## Results

Recruitment for the trial started in January 2019. As of July 2019, we have enrolled 120 participants. Data collection is expected to be completed by March 2020. Once all the data have been collected, we will conduct the data analyses between April and May 2020. We aim to publish our results in a manuscript by June 2020.

## Discussion

In this paper, we outlined the design of an RCT to examine the effectiveness of iSupport for families and other unpaid carers of people with dementia in improving their mental health and coping strategies.

iSupport was developed by the WHO for global implementation and therefore includes guidelines for translation and cultural adaptation of the intervention. Internet interventions are a promising channel to prevent or treat mental health conditions of relatives and other unpaid carers who face greater risk of experiencing mental health problems themselves [41]. iSupport may increase unpaid carers’ worldwide accessibility to the support they need through the internet. An advantage of the intervention is that it is flexible and carers can decide which lessons they want to complete. Another advantage is that it can be provided with no or minimal professional support. This enables upscaling of the intervention without high costs. It might fit into a stepped-care model, in which only the carers who need more support are stepped up to face-to-face interventions. Additionally, family and other unpaid carers go through different stages during the course of dementia; their needs and preferences for training and support may substantially vary accordingly [42,43]. iSupport contributes to enriching and completing a continuum of interventions addressing the needs of carers in the Netherlands. This continuum should cover interventions from face-to-face to online interventions as well as guided to self-help interventions and everything in between.

The fact that the intervention is offered with minimal support might not only be a strength but also a weakness. It might lead to higher dropout rates. A review on the treatment adherence of online interventions carried out in 2008 [44] shows that in some trials participants never accessed the interventions tested, while others used them inconsistently. We try to minimize that risk by providing personalized automated feedback in iSupport as well as via periodic contact with e-coaches and the option to consult the e-coach more frequently. Hopefully, this encourages carers to continue with the intervention.

To the best of our knowledge, this is the first randomized trial for a minimally guided online intervention focusing on mental health outcomes for family and other unpaid carers of people with dementia in the Netherlands. This will provide valuable information for the Netherlands, but it will also contribute to the evidence for the use of iSupport at a global scale. An RCT of the Indian version of iSupport began in 2017 [19], and it is expected that more adaptations of iSupport will be completed worldwide in the future. We will test the effect of the intervention on different types of outcomes. Our study will try to overcome the possible challenges of RCTs of minimally guided online interventions, for example, by including personalized automated feedback. With our online and offline recruitment procedure, we expect to find a heterogeneous group of carers. Finally, the inclusion of a waiting list control group will allow all participants to benefit from the online tool.

In conclusion, using a two-arm RCT, our study will provide valuable information about the effectiveness of a minimally guided online intervention tool on participants by comparing outcomes with a waiting list control group. If the results of this study are satisfactory, iSupport may be a valuable response to an existing demand of carers for support in the Netherlands.

## Appendix

Multimedia Appendix 1 Peer-reviewer report from the European Commission.

## Abbreviations

AD8: Ascertain Dementia 8-item informant questionnaire
ADQ: Approaches to Dementia Questionnaire
AN: Alzheimer Nederland
CBT: cognitive behavioral therapy
CES-D: Centre for Epidemiological Studies Depression scale
CONSORT: Consolidation Standards of Reporting Trials
HADS-A: Hospital Anxiety and Depression Scale-Anxiety subscale
INDUCT: Interdisciplinary Network for Dementia Using Current Technology
ITN: Innovative Training Network
N/A: not applicable
PMS: Pearlin Mastery Scale
PSS: Perceived Stress Scale
RCT: randomized controlled trial
RIS: relational self-efficacy, instrumental self-efficacy, and self-soothing efficacy
SSCQ: Short Sense of Competence Questionnaire
SUS: System Usability Scale
T0: baseline assessment
T1: 3-month follow-up assessment
T2: 6-month follow-up assessment
WHO: World Health Organization
ZBI: Zarit Burden Interview
